#### Outcome measures

The primary and secondary outcomes are listed in Table 1 for each study aim. Data collection tools and relevant timepoints of measurement for the clinical, process and economic evaluation are outlined in Table 2.

**Table 1 Tab1:** Primary and secondary aims and trial outcome measures

**Primary aims**	**Primary Outcomes**
Trial feasibility	
Acceptability	The proportion of participants that: • Complete the feasibility trial • Attend the follow-up service (intervention group)
Participant, service coordinator and clinician satisfaction^a^	Satisfaction and experiences of participants and service coordinators (+ / − other clinicians at participating health services) with the hospital-led follow-up service, assessed through project documentation, field notes, surveys and/or interviews/focus groups
**Secondary aims**	**Secondary outcomes**
Potential clinical effectiveness, i.e. health status	Health-related quality of life (EQ-5D-3L survey [19]) including change in the proportion with extreme health problems at 12–14 week post-randomisation. Also composite outcome: extreme health problems reported on EQ-5D-3L [19] or visual analogue scale score 60 points or less
	Unmet needs: Longer-Term Unmet Needs Survey [22]
	Unplanned emergency department presentations and/or admissions to hospital (self-reported)^b^
	Disability (modified Rankin scale [20])
Healthcare service utilisation^b^	Use of health and community services (self-reported)
	Change in medications (self-reported)
Cost implications of the programme^b^	Costs of intervention delivery (self-reported) Cost or cost offsets from health and community services used (self-reported)

^a^Will be included in the process evaluation

^b^Will be included in the economic evaluation and converted to costs

**Table 2 Tab2:** Data collection tools for clinical, process and economic evaluation across trial timepoints

**Project stage**	**Measure**	**Measurement tool**	**Completed by**	**Pre-trial, eligibility**	**Baseline**	**During 12-week intervention**	**12–14 weeks-outcome assessment**	**Post-trial**
Identifying eligible participants	Ongoing health problems impacting quality of life, disability/dependence and living situation^a^	AuSCR follow-up survey including EQ-5D-3L [19], modified Rankin Scale (mRs) [20] and current residence	AuSCR registrant 90–180 days poststroke	X				
Clinical evaluation	Quality of life^b^	EQ-5D-3L (baseline: to verify responses from pre-trial is still current, and eligibility is still met for the service)	All participants in conjunction with blinded AuSCR follow-up team member		X		X	
	Disability/dependence^b^	mRS (baseline: to verify responses from pre-trial is still current, and eligibility is still met for the service) Communication and fatigue (yes/no and 5-point Likert scale, respectively)			X		X	
	Unmet needs	Longer-Term Unmet Needs for Stroke questionnaire [22]			X		X	
	Unplanned hospital readmissions, ED visits^b^	Survey tailored for A-LISTS trial			X		X	
	Serious adverse events^b^	Serious adverse events form specific for A-LISTS trial				X	X	
	Health service use diary for participants	Developed for trial to support recall; used as memory aid at the outcome assessment to respond to questions about current health services used	All participants			X		
Process evaluation	Satisfaction & experiences with service and study participation	Theory-informed survey and/or semi-structured interview/focus groups	Intervention participants				X	
	Satisfaction with service, including implementation features & intervention fidelity	Theory-informed survey and semi-structured focus groups [23, 24]	Service coordinator and clinicians					X
	Participation numbers, recommended actions, uptake of service coordinator recommendations	Template tailored for A-LISTS study; patient-level data will be aggregated	Service coordinator			X		
	Project documentation	Standard operating procedures, minutes, training documents, project notes	Project team, investigators	X	X	X	X	X
Economic evaluation	Current health services used, medications, costs^b^ Programme delivery costs	Resource use questionnaire developed for trial Research (financial) documents, invoices			X		X	

*Abbreviations*: *AuSCR* Australian Stroke Clinical Registry, *EQ-5D-3L* EuroQol 5-dimension 3-level survey; *mRS*, modified Rankin Scale

^a^Standard Australian Stroke Clinical Registry follow-up survey completed 90-180 days after admission

^b^indicates data will also be used for the economic evaluation

### Description of secondary outcome clinical effectiveness measures

Secondary outcome measures relating to the measurement of HRQoL, unmet needs and disability are described below.

#### HRQoL measured by EQ-5D-3L and Visual Analogue Scale

The EQ-5D-3L [19] is a standardised instrument developed by the EuroQol group to measure health-related quality of life and is widely used internationally and by the AuSCR. It comprises five dimensions: mobility, self-care, usual activities, pain/discomfort and anxiety/depression. Each dimension is self-reported by participants to indicate no problems, some problems or extreme problems. The EQ-5D-3L also includes a VAS. The VAS ranges from 0 (worst imaginable health state) to 100 (best imaginable health state). The median VAS reported by patients post-stroke in Australia is 70 [7], and a normative median score from a similar population without stroke is 80 [25].

#### Longer-term Unmet Needs after Stroke (LUNS) questionnaire

The LUNS questionnaire is a 22-item tool that enables the collection of the longer-term problems affecting the physical, psychological and social facets of people living with stroke [22]. It can also be used as a tool to evaluate community service usage and whether those community services are meeting the person’s needs [25]. Most studies have used the LUNS between 3 and 6 months post-stroke; however, it has been used up to 5–8 years following stroke [26]. The LUNS is acceptable to people living with stroke and has satisfactory validity and test–retest reliability [22].

#### Modified rankin scale (mRS) scale

The mRS is a single-item, global disability rating scale [20] often used in stroke trials for assessment of patient outcomes [27]. The categorical scale is as follows: 0 = no symptoms at all, 1 = no significant disability despite stroke-related symptoms, 2 = stroke-related disability but remains functionally independent, 3 = functionally dependent but independently mobile, 4 = requires assistance to mobilise and 5 = requires constant care and is bed-bound [28]. For this study, the mRS outcome will be dichotomised into two groups (0 to 2 [independent] vs dependent/dead [mRS 3 to 6]).

#### Sample size

Up to 100 people with stroke will be recruited (50 for intervention and 50 for control), which is consistent with recommendations for pilot and feasibility studies [29, 30]. It is anticipated that each participating hospital will provide the intervention to approximately 10–15 people, with a capacity of providing the follow-up service to 1–2 intervention participants per week.

#### Ethics

Ethics approval for this project was obtained by the Austin Health Human Research Ethics Committee (HREC/89487/Austin-2022). Hospital-specific governance approval will also be obtained from participating hospitals. Approval for the use of the existing AuSCR data has been obtained from the AuSCR Steering Committee, the governing body of AuSCR.

### Treatment groups

#### Intervention

Participants in the intervention group will receive the tailored follow-up service implemented over 12 weeks. The service coordinator will be provided with a tailored patient referral report (including demographic and clinical data collected from the baseline assessment). The intervention follow-up service utilises clinicians’ clinical reasoning and experience to help participants navigate the hospital, community and primary care systems. This support may include linking participants to appropriate locally available services. All service coordinators will have a clinical background in stroke (e.g. stroke nurse, stroke allied health) and will receive 4–8 hours of training tailored to the hospital setup. The service coordinator will conduct an initial assessment with the participant (either in-person or via telehealth; participant’s choice) to ascertain existing service usage and how to assist the participant with their unmet needs. Through a collaborative and shared decision-making approach with the participant, the level of input required will be tailored to the participant’s needs. The service coordinator will then organise referrals as required and provide advice and education as necessary.

Following the initial consultation, there are six possible scenarios (Fig. 2). Only existing and available services or treatments will be offered in the trial. The intervention follow-up service will be tailored to the individual participant. It does not dictate how often or which clinicians or services will have ongoing engagement with participants over the 12-week intervention period. Participants will be asked for their permission to share information with their general practitioner (GP) including the purposively designed A-LISTS GP letter. Depending on the participant’s age, location, needs, priorities and healthcare network, we envisage that some participants may be referred to services such as allied health services (e.g. physiotherapy, occupational therapy), community rehabilitation programmes and state-funded community health programmes (e.g. chronic disease management plan [31]). The service coordinator may also liaise with the National Disability Insurance Scheme [32], My Aged Care [33] and other stroke resources (e.g. Stroke Foundation services and information) to help participants navigate the system and provide education.

There will be no charges to participants for accessing the follow-up service, although some private services participants are referred to may incur fees. As this is an embedded real-world health services trial, we will utilise existing private, public, free and online services. Research funding will not be used to cover other out-of-pocket expenses (i.e. allied health services, specialist visits). Participants will be provided with an electronic or paper diary, to record health and community care contacts and referrals including dates and reasons for health and community care visits, to assist with completing the trial outcome assessment conducted at 12–14 weeks. The service coordinator is to record their notes as soon as possible after the service is delivered and ensure the letter using the template is sent to the GP.

#### Control group

Participants in the control group will receive their usual care (e.g. existing services or supports) in the community. They will also be provided with an electronic/paper diary to record health and community care contacts and referrals used to complete the outcome assessment conducted 12–14-weeks post-randomisation. At the end of the trial, information about participants in the control group who will be assessed as having ongoing high levels of unmet needs will be passed to the hospital team, who may choose to offer follow-up within current services available to them.

#### Safety monitoring

Occurrence of serious adverse events (SAEs) will be documented throughout the feasibility RCT by the service coordinator and blinded outcome assessor. Relevant information will be obtained from the participant and/or proxy and hospital medical records (where possible by the service coordinator accessing the medical records). SAEs are defined as any untoward or serious medical occurrence that results in death, life-threatening incidents, hospitalisations, an event that results in new disability/incapacity, or other important medical events [34]. SAEs will be reported to a neurologist who will act as the medical monitor (author [name]) for adjudication. If the SAE is deemed to be related to the study intervention, then a report will be submitted to the ethics committee and the local research governance office.

#### Process evaluation

The process evaluation draws on implementation evaluation theory and models including the Medical Research Council guidance for complex interventions [35] and Normalisation Process Theory [36]. The process evaluation includes mixed methods since qualitative data in feasibility studies helps to refine the understanding of how the intervention works and facilitate ongoing adaptation of the intervention and evaluation design in preparation for a larger trial [37]. Data will be collected using project documentation, field notes, surveys and interviews/focus groups as outlined below.

#### Satisfaction survey

All participants will be invited to complete an electronic/paper satisfaction survey (including open and closed questions) at the 12–14-week post-randomisation outcome assessment. Information on satisfaction and experience with the care received in the community will be obtained, with specific questions related to the service coordinator and follow-up service also included for those in the intervention group. The service coordinator (and any other clinicians involved in the initial consultation) will also be invited to complete a survey exploring their experience of implementing and delivering the follow-up service.

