#### Interviews/focus groups

At the conclusion of the RCT, semi-structured focus groups/interviews (*n* = 3, 6–10 in each group, with up to 30 people in total) will be undertaken with groups of the following: (i) clinicians involved in delivery of the service (all service coordinators and up to two other purposively selected clinicians per hospital if they were involved) and (ii) purposively selected participants, based on satisfaction variation from survey results, to further explore the facilitators and barriers to service implementation and delivery. Examples of questions are provided in Table 3.

**Table 3 Tab3:** Example questions and prompts for focus-group interviews^a^

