#### Prespecified criteria to judge proceeding with future definitive trial

Various aspects of this trial (participant-level data, process evaluation and economic evaluation data) will provide evidence to support the investigators in making changes to the protocol and in the determination of whether we proceed to a definitive trial based on the current or a modified format. For progression, we anticipate the following: recruit at least 25% of potentially eligible participants, consent at least 40% of people identified as eligible and who agreed to participate, > 80% retained, > 70% adherence to core study protocol components (i.e. intervention group participation in the initial consultation), complete data for 80% of primary and secondary health outcome surveys, at least 30% with a positive change in health status from baseline (i.e. fewer unmet needs or extreme problems reported at 12-week EQ-5D-3L), no serious adverse events related to the study intervention or other procedures, > 60% satisfied and would recommend the trial to others (with a larger proportion in the intervention group). Ability to recruit hospitals (> 70% that indicated willingness and progressed to site-specific ethics participated) and the resources to conduct a future trial will also be important criteria for progression.

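### Participant satisfaction is surveyed only at 12–14 weeks and interviewees are picked from that survey, so people who leave the trial earlier give no direct view and the > 60% criterion can be biased upwards

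*Protocol article*

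**What the plan says.** Table 1 of the protocol article lists "Satisfaction and experiences of participants and service coordinators" with the follow-up service among the primary outcomes, "assessed through project documentation, field notes, surveys and/or interviews/focus groups". The abstract equates acceptability with the satisfaction of the clinicians and participants involved in the intervention. Table 1 instead sets acceptability beside two proportions: those who "Complete the feasibility trial" and, in the intervention group, those who attend the service.

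The Satisfaction survey section gives the participant survey one time point: "All participants will be invited to complete an electronic/paper satisfaction survey (including open and closed questions) at the 12–14-week post-randomisation outcome assessment". Table 2 shows the same single time point, although it names intervention participants only. Service-specific questions are added for the intervention group.

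The Interviews/focus groups section draws its participant interviewees as "purposively selected participants, based on satisfaction variation from survey results", within a total of up to 30 people that also includes clinicians.

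The section on prespecified progression criteria requires more than "60% satisfied and would recommend the trial to others", with a larger share in the intervention group. It states no denominator. Separate criteria ask for > 80% retained and > 70% adherence, the latter meaning participation in the initial consultation.

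**The concern.** Leaving a trial of a service can be a sign that the service was not acceptable. A survey given only at the end reaches those still present, and an interview sample taken from its results carries the same selection into the qualitative data. If the people missing are less satisfied than those who reply, the satisfaction percentage is too high, and the interviews on barriers do not include the people for whom the barriers mattered most.

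Two things are at stake: a primary outcome, and one of the criteria for going on to a definitive trial. A later analysis plan could settle the denominator, but it could not recover views that nobody asked for.

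A smaller mismatch lies in the same criterion. It asks whether people would recommend the trial, whereas Table 1's outcome is satisfaction with the service.

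**Working it through.** The protocol gives no derived figure to reproduce. The check is one of denominators.

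**Inputs**
- Arm size 50 (Sample size: "Up to 100 people with stroke will be recruited (50 for intervention and 50 for control").
- Retention criterion > 80%, so the smallest passing number in one arm is 41 (41/50 = 82%).
- Satisfaction criterion > 60%, denominator not stated.
- Assumption: the criterion is read over survey respondents, and either all or 80% of those retained reply. The 80% is my figure, not the protocol's.

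**Formula.** With m respondents, the smallest passing count is s = floor(0.6 × m) + 1. The share of those allocated who are known to be satisfied is s/50. If every non-respondent were satisfied, the share would be (s + 50 − m)/50.

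| Retained | Replying (m) | Smallest passing s | s/m | Known satisfied, s/50 | If all missing were satisfied |
|---|---|---|---|---|---|
| 50 | 50 | 31 | 62% | 62% | 62% |
| 45 | 45 | 28 | 62.2% | 56% | 33/50 = 66% |
| 41 | 41 | 25 | 61.0% | 50% | 34/50 = 68% |
| 41 | 33 (0.8 × 41 = 32.8) | 20 | 60.6% | 40% | 37/50 = 74% |

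With no loss the two denominators agree. At the retention limit with full response, the criterion passes while the share of the arm that is satisfied could lie anywhere from 50% to 68%.

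If the criterion were instead read over all 50, it would need 31 satisfied. With 41 respondents that is 31/41 = 75.6%, so the choice of denominator moves the bar a long way.

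**Do the other criteria close the gap?** Take an intervention participant who attends the first consultation, dislikes the service and leaves the trial in week 4.
- Adherence: counted as adherent, because the criterion is the initial consultation.
- Retention: one of the losses that the > 80% limit tolerates.
- Satisfaction survey: none, because it is given at 12–14 weeks.
- Interview: no stated route, because selection uses survey results.
- Staff account: possible, since a Table 3 prompt asks service coordinators and/or registry staff about people who withdrew or refused.

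Retention shows that this person left. Nothing described collects the reason from the person directly.

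**The case against.** The strongest reply is that withdrawal is already measured. Completion and attendance are primary outcomes, completion is compared between groups, and retention and adherence have their own criteria. A reader might infer that people who withdraw are never counted or heard. The documents do not support that: each withdrawal lowers completion and retention, and staff prompts, field notes and project documentation give indirect information.

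Leaving the service is also not the same as leaving the trial. The survey invitation goes to all participants, so someone who drops the service but stays in the trial can report dissatisfaction and be chosen for interview. Only those who leave the trial lack a direct response, and some of these losses will be deaths or illness that say nothing about satisfaction.

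The table combines minimum retention with minimum satisfaction and counts no non-respondent as satisfied. Its last row has 33/50 = 66% returning the survey. That would fail the criterion of complete data for 80% of outcome surveys if that criterion covers the satisfaction survey, which its wording leaves open. The row with 41 respondents (82%) would not fail it.

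Counting every non-respondent as dissatisfied would penalise losses that retention already counts. Rewording the item to recommend the service would not work for controls, who receive no such service. Both points stand and shape the fix.

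Finally, a condensed article may leave withdrawal procedures to a fuller document. That is fair for the denominator and for exit procedures in general. The survey's timing and the interview sampling frame, however, are stated here, and as stated they leave the gap.

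**Conclusion.** The point holds as one about the satisfaction component, its > 60% criterion and the interview sample. People who leave the trial before 12–14 weeks have no direct satisfaction response and no stated route to interview, so this component is open to upward bias from selection of those who stay and reply.

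The size is a bound, not an estimate. With 41 of 50 retained and all replying, the criterion can pass with 50% of the arm known to be satisfied. If only 33 reply, the figure is 40%. Both rest on a respondent denominator, on satisfaction just over the threshold and, for the second, on an assumed 80% response.

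A reader might go further and conclude that acceptability is overstated. The documents do not show that. The bias depends on how many leave and whether they are less satisfied. Table 1's acceptability entry also includes completion and attendance; every loss from the trial lowers completion. This is a change worth making to a feasibility design, and it does not undermine the trial.

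**What to change.** 1. **Interviews/focus groups:** select participants on service attendance and withdrawal status as well as satisfaction score. Include people who declined or left the service or the trial and agree to be contacted. Keep the total at up to 30.
2. **Satisfaction survey:** keep the 12–14-week survey and offer the short survey, optionally, at the time of withdrawal.
3. **Progression criteria:** report the satisfaction proportion among respondents together with a conservative figure over all randomised in each arm, in which non-responders are not counted as satisfied. Judge the criterion in light of both, and do not make the conservative figure the sole rule.
4. **Item wording:** keep the between-arm item on recommending the trial. For the intervention arm, also report the service-specific satisfaction questions already collected, since these match Table 1's outcome.

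The cost is some extra contact work, amended wording and a less favourable satisfaction figure. The Trial status section reports 50 participants randomised on 1 May 2024 with recruitment unfinished, so at that point the change could still apply to much of the sample.
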